### 10.3.2 Primary Analyses

The primary endpoint (i.e., the ratio of covered area to biopsy site / donor site surface area at 4 weeks post grafting) will be tested with a one-sample t-test applied on the difference between  $\log(\text{ratio})$  EHSG-KF and  $\log(\text{ratio})$  STSG. The treatment effect estimate and its 95% confidence limits obtained on the logarithmic scale will be expressed as percentage of increase of EHSG-KF relatively to STSG by applying the transformation  $[x \rightarrow (x-1) \cdot 100]$ . A claim of study success will be made when the two-sided test of the primary endpoint passes the significance level of 0.05.

As a robustness analysis, the difference between  $\log(\text{ratio})$  EHSG-KF and  $\log(\text{ratio})$  STSG will also be tested with one-sample Wilcoxon test (signed-rank test). The corresponding treatment effect estimate and its 95% confidence limits will be derived from the median of this difference by applying the transformation  $[x \rightarrow (x-1) \cdot 100]$ .

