### **1.1.2 Clinical Summary**

The present proposal is based on the successful completion of the phase I clinical trial in which EHSK-KF was safely grafted as an autologous skin substitute for the reconstruction of burn scars and congenital nevi, and for the coverage of an acute burn, in 10 paediatric patients.

The primary endpoint was safety, as determined by the rates of local infection and graft take. There were no cases of infection, and graft take was acceptable. The mean graft take rate was 63.5% overall (median 78.0%, range 0-100%, SD 36.5%) and 70.6% (range 5-100%, SD 30.6%) when excluding one patient with 100% graft loss attributable to mechanical disruption of the graft post-operatively. Healed skin analogues have been stable thus far without blistering or breakdown.

There were three adverse events deemed to be possibly related to the study product/treatment. There were three severe adverse events (SAE), one that was deemed to be 'unrelated' to the study product/treatment and two that were deemed to be 'possibly related', but importantly all three of these SAEs are also expected complications of conventional grafting surgery. There were no suspected unexpected serious adverse reactions.

In addition, the healed EHSK-KF yielded high quality scars and excellent tissue elasticity, as supported by the POSAS scores. These findings further substantiate the preclinical animal and laboratory studies, supporting EHSK-KF as a viable skin substitute. The clinical phase of the study took place over two years (June 2014-June 2016), and long-term follow-up assessments were carried out annually for five years post grafting concluding in March 2021. For further details please refer to the IB.

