#### **4.3.3 Replacement of Patients**

The following points describe the procedure of replacement/enrolment of patients:

- Drop-out prior to grafting: Patient is replaced
- Drop-out after grafting: Patient is not replaced

Patients will continue to be enrolled in the study until 12 patients were evaluated for primary endpoint (visit 6) (see chapter 10.2).

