### 10.2 Determination of Sample Size

The primary endpoint (i.e. the ratio of covered surface area to biopsy site / donor site surface area at 4 weeks post grafting) will be analysed after a logarithmic transformation and the treatment effect estimate will be expressed as a percentage of additional coverage obtained with EHSG-KF comparatively to STSG.

Published data of cultured skin substitutes in a series of 10 patients (Boyce 1995, Table 11) show on the logarithm of the ratio of covered surface area to biopsy site surface area (also named expansion ratio) at 1 month post grafting a standard deviation of 0.97 with a mean of 1.98 (corresponding to a geometric mean of 7.24 on the original scale). Data from the EHSG-KF Phase I clinical trial (excluding one patient with 100% graft loss attributable to patient noncompliance and manipulation of the dressing post-operatively) show on the logarithm of the ratio of covered surface area to biopsy site surface area at 3 weeks post grafting a standard deviation of 0.99 with a mean of 1.80 (corresponding to a geometric mean of 6.05 on the original scale). A standard deviation of 1.00 will be assumed for the difference (on the logarithmic scale) between the two treatments, corresponding, for instance, to a common standard deviation of 1.00 on each treatment site with a correlation between sites of 0.50.

The ratio of covered surface area to biopsy site / donor site surface area at 4 weeks post grafting is expected to be at least 145% higher on EHSG-KF than on STSG (corresponding, for instance, to ratios of 7.35 and 3.00, respectively).

- Assuming a standard deviation of 1.00 for the paired difference between the 2 log(ratios), a sample size of 12 evaluable patients would be required in order to achieve a power of 80% to detect a treatment effect corresponding to an increase of 145% with EHSG-KF (i.e. to a difference of 0.90 on a logarithmic scale) when using a one-sample t-test at two-sided significance level of 5%.  
A claim of study success will be made when the two-sided test passes the significance level of 0.05.
- All secondary endpoints will be tested in a strictly exploratory fashion only.

**Table 11:** Criteria for sample size determination

| Criteria                                                                                   | Value |
|--------------------------------------------------------------------------------------------|-------|

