## 10.3 Planned Analyses

### 10.3.1 Analysis Populations

Since randomization takes place during the operation procedure (or shortly before, as described in chapter 3.5), it is assumed that there is no difference between "randomized" and "treated" patients. Therefore, the following analysis populations are defined.

mITT (modified ITT) population: consists of all randomized/treated patients having at least 1 post-surgical measurement. The mITT population will be used for the analysis of efficacy variables, and statistical analysis will be done "as randomized".

PP (per protocol) population: consists of all patients adhering to the protocol. The PP population is subset of the mITT population. Subjects with major protocol deviations that might impact the primary endpoint will be excluded from this population. These deviations will be

determined before database lock. The PP population will be used for the analysis of efficacy variables, and statistical analysis will be done “as randomized”.

SAF (safety) population: includes all patients who have received a surgical treatment, irrespective of satisfying other criteria. This population will be used for the analysis of safety and tolerability, and statistical analysis will be done “as treated”.

The primary analysis will be performed using the mITT as primary analysis population, and PP as supportive. Secondary and exploratory efficacy analyses will only use the mITT. Safety analyses will be presented using the SAF.

Implications of administration of OOS products (see chapter 3.2.8) on analyses are expected to be minimal considering that only OOS products with a positive risk/benefit ratio on patient safety will be administered. Data of patients with OOS products administered are included in the analyses.

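### The primary log-ratio tests have no rule for a study area with zero covered surface at visit 6, although the protocol foresees total EHSG-KF loss and keeps such patients in the mITT

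*Protocol*

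**What the plan says.** - **Test.** Protocol 10.3.2: the ratio of covered area to biopsy or donor area at 4 weeks "will be tested with a one-sample t-test applied on the difference between" log(ratio) for EHSG-KF and log(ratio) for STSG. The only robustness analysis is a signed-rank test on the same log difference. Study success rests on the two-sided 5% t-test.
- **Numerator.** Section 8.1.1 counts only healed or epithelialized surface and leaves out open wound. Section 7.3.8 counts parts that have epithelialized as well as parts covered by healed product.
- **Population.** Section 10.3.1: the mITT is primary and "consists of all randomized/treated patients having at least 1 post-surgical measurement". Membership does not require a non-zero ratio.
- **Foreseen failure.** Section 4.3.2 withdraws patients with complete loss of EHSG-KF only after the one-year visit, so they are still in the study at visit 6.
- **Planning.** Section 10.2: "a sample size of 12 evaluable patients would be required in order to achieve a power of 80" per cent, for "a difference of 0.90 on a logarithmic scale" and an SD of 1.00, with a "one-sample t-test at two-sided significance level of 5" per cent. The supporting phase I log mean (1.80) and SD (0.99) were computed "excluding one patient with 100% graft loss attributable to patient noncompliance and manipulation of the dressing post-operatively".
- **Phase I.** Section 1.1.2, on 10 patients: "The mean graft take rate was 63.5% overall (median 78.0%, range 0-100%, SD 36.5"%).
- **Enrolment.** Section 4.3.3: "Patients will continue to be enrolled in the study until 12 patients were evaluated for primary endpoint (visit 6").

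**The concern.** The protocol fixes the transformation, the test, the population and the success criterion, and these cannot all be applied to an outcome that it foresees. A patient with no epithelialized surface on one side belongs to the mITT but has no log difference, and so has no place in the t-test or in the test meant to check it. Nothing in the protocol supplies a value, a rank or an exclusion for this case.

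The planning step had a total-loss patient in its source data and set that patient aside; the analysis section is silent on the same event. With 12 patients in an open-label trial, and with an interim test of the primary endpoint allowed under 10.1.3, a rule chosen after the data are seen could decide the result through a single patient.

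**Working it through.** **1. The plan's own figure.** Inputs from 10.2: difference 0.90, SD 1.00, n = 12, two-sided 5%. One-sample t-test power from the noncentral t, with df = 11 and noncentrality 0.90 × √12 / 1.00 = 3.12, is 0.81. With n = 11 it is 0.77, so 12 is the smallest n that reaches 80%. The stated figure is right for 12 patients who all have a defined log ratio.

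**2. What the phase I figures contain.** A mean take of 63.5% over 10 patients, with one of them at 0%, gives 63.5 × 10/9 = 70.6% for the other nine. That matches the mean which 1.1.2 gives without the total-loss patient. So one of 10 had 0% graft take, and 10.2 excludes a patient with 100% graft loss from the log mean and SD.

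**3. Chance of at least one zero.** With rate p and independent patients, it is 1 − (1 − p)^12:
- p = 5%: 1 − 0.95^12 = 46%
- p = 10%: 1 − 0.90^12 = 72%

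These rates are assumptions. The documents give no rate of zero covered area on either side.

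**4. If zeros are dropped.** If they are not made up from 12 grafted patients, power is 78% (p = 5%) or 75% (p = 10%). If enrolment continues to 12 defined values, power stays at 0.81. The reported effect then stays near exp(0.90) = 2.46, or +146%, and describes only patients without a zero.

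**5. If zeros are kept at a floor value.** Assumptions: failures on the EHSG-KF side only, biopsy 4 cm², STSG ratio 3.00, other patients N(0.90, 1.00). A failure then contributes d = ln(floor/4) − ln(3.00), and the geometric mean ratio is exp[0.90(1 − p) + p·d]. Power is simulated for n = 12.

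| Floor (cm²) | d | Power, p = 5% | Power, p = 10% | Geometric mean ratio, p = 10% | Power, exactly one zero in 12 |
|---|---|---|---|---|---|
| 0.45 | −3.28 | 45% | 24% | 1.62 | 4% |
| 1 | −2.48 | 50% | 29% | 1.75 | 17% |
| 2 | −1.79 | 56% | 37% | 1.88 | about 35% |

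**6. Signed-rank test with worst rank.** With no failure, simulated power is about 77–78%. With exactly one failure ranked as the most extreme negative, it is about 16–18%. The reason is simple: for n = 12 the two-sided 5% test needs a negative rank sum of at most 13, and one worst-ranked failure already uses 12.

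**The case against.** Several stronger readings are tempting, and the documents do not support them.

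- *That failures are deleted.* No section says so. The handling is undefined; omission is what software does with a missing log, and an analysis plan that is not shown may set a rule. Bias towards EHSG-KF is therefore conditional. A zero on the STSG side would act the other way, and no STSG loss rate is given.
- *That total graft loss means zero covered area.* It need not. Section 7.3.8 counts any epithelialized part, and 7.3.5 allows conservative or surgical closure after poor take. The phase I 1 in 10 is a graft-loss rate, not a rate of undefined logs, so the 72% is an illustration at an assumed 10%.
- *That the phase I patient was removed because the log did not exist.* Section 10.2 gives noncompliance and dressing manipulation as the reason.
- *That the 80% is wrong.* It reproduces, and it is stated for evaluable patients. The low powers in step 5 come from an assumed rate and an assumed floor, not from the protocol's test as written.
- *That enrolment replaces failures.* Section 4.3.3 does not replace drop-outs after grafting, and nothing says that a patient with a zero is not evaluated.
- *That failures vanish from the efficacy results.* Percentage epithelialization, graft take and wound closure all accept a zero and are analysed on the mITT.

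It is also fair that conventions for zeros before a log are often left to the analysis plan. That carries less weight here, because 10.3.2 itself fixes both tests on the log scale, and the explicit deferral in 10.3.3 concerns the secondary and exploratory models. The gap in 10.3.2 stands.

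**Conclusion.** The point holds in this form: the two tests named in 10.3.2 cannot be applied to the mITT of 10.3.1 if any study area has zero covered surface at visit 6, and the protocol foresees the kind of failure that could produce one. The arithmetic of the 80% is correct (0.81). Its scope is narrower than the mITT, since it assumes that every patient has a defined log ratio.

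The size cannot be fixed from the documents because the zero rate is unknown. What can be said is how sensitive the trial is. One zero among 12 takes t-test power from 81% to between 4% and about 35%, depending on the floor, and signed-rank power from about 77–78% to about 16–18%. Dropping the same patient leaves power near its stated level. The unstated rule can therefore decide the trial. These figures assume the planning values for all other patients, failure on the EHSG-KF side only and, for the t-test, an STSG ratio of 3.00 and a 4 cm² biopsy.

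**What to change.** In 10.3.2:
- State that a patient with zero covered area on either side stays in the mITT and counts as evaluated under 4.3.3.
- In the signed-rank test, rank that patient as the most extreme result against the failed side. This needs no invented area.
- If the log t-test stays primary, prespecify one small covered-area value (for example the smallest measurable area) and show results over a range of values that includes it. The table in the working shows how strongly the constant drives the result, so it must be set before any primary-endpoint data are extracted, including for the interim analysis in 10.1.3.

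In 10.2, state that the 80% holds for 12 patients with no zero covered area, and give illustrative power at 5% and 10% zeros.

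The cost is wording only: no new data and no change to conduct. The stated power, and possibly the estimate, become less favourable.

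### The back-transformation of the primary effect omits the exponential: the planned log difference of 0.90 would be reported as -10% instead of about +146%

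*Protocol*

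**What the plan says.** Section 10.3.2 (Primary Analyses) states that the primary endpoint "will be tested with a one-sample t-test applied on the difference between" the log ratio on EHSG-KF and the log ratio on STSG. The estimate and 95% limits "obtained on the logarithmic scale will be expressed as percentage of increase of EHSG-KF relatively to STSG by applying the transformation" x -> (x-1)*100. The robustness paragraph, which uses the Wilcoxon signed-rank test, gives the same rule: "The corresponding treatment effect estimate and its 95% confidence limits will be derived from the median of this difference by applying the transformation" x -> (x-1)*100. Neither paragraph mentions taking the exponential.

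Section 10.2 (Determination of Sample Size) says that the effect will be reported as a percentage of extra coverage. It plans for "an increase of 145% with EHSG-KF (i.e. to a difference of 0.90 on a logarithmic scale"), and says that the primary ratio "is expected to be at least 145% higher on EHSG-KF than on STSG (corresponding, for instance, to ratios of 7.35 and 3.00, respectively").

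**The concern.** The quantity x that enters the formula is, by the protocol's own description, a mean (or median) difference of logarithms with its limits. The expression (x-1)*100 turns a ratio into a percentage change; applied to a log difference it has no such meaning. On the log scale no effect is x = 0, and the formula sends 0 to -100%. It returns a positive figure only when x exceeds 1, which is a ratio above exp(1) = 2.72 and so more than the 2.45 the trial was designed to detect. For any x below 0 it gives a fall of more than 100%, which is impossible for a ratio of areas.

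This percentage is the form in which the protocol says the primary result will be presented. If the rule were followed, the reported effect could have the wrong sign and its interval could disagree with the p-value beside it. The figure may also be needed early: section 10.1.3 allows the primary endpoint to be analysed at an interim on the first 12 treated patients to support a request for a regulatory designation.

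**Working it through.** **Inputs (all from section 10.2)**

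- Planned log difference: 0.90, equated with +145%.
- Example ratios: 7.35 on EHSG-KF and 3.00 on STSG.
- SD of the paired log difference: 1.00.
- Test: one-sample t-test, two-sided 5%, 80% power, 12 evaluable patients.
- Pairs of log mean and geometric mean: 1.98 with 7.24, and 1.80 with 6.05.

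**Step 1: reproduce the plan's own figures**

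- Log base: exp(1.98) = 7.24 and exp(1.80) = 6.05, so natural logs are used.
- Effect: 7.35/3.00 = 2.45, which is +145%; ln(2.45) = 0.896, rounded to 0.90.
- Sample size: the exact noncentral-t power is 76.7% with 11 patients and 81.0% with 12, so 12 is the smallest adequate number and is confirmed.

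The link between 0.90 and 145% in section 10.2 therefore works only through (exp(x)-1)*100.

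**Step 2: point estimate under each rule, x = 0.90**

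- As printed: (0.90 - 1)*100 = -10%.
- With the exponential: (exp(0.90) - 1)*100 = (2.460 - 1)*100 = +146%.

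The gap between 146% and 145% is only the rounding of 0.896 to 0.90.

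**Step 3: confidence interval if the planning values are observed exactly**

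- Test statistic: 0.90*sqrt(12)/1.00 = 3.12 on 11 degrees of freedom, p = 0.0098.
- Half-width on the log scale: t(0.975, 11)*1.00/sqrt(12) = 0.635.
- Log-scale limits: 0.90 - 0.635 = 0.265 and 0.90 + 0.635 = 1.535.

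| Log-scale value x | As printed, (x-1)*100 | With exponential, (exp(x)-1)*100 |
|---|---|---|
| Lower limit 0.265 | -73.5% | +30.3% |
| Estimate 0.90 | -10.0% | +146.0% |
| Upper limit 1.535 | +53.5% | +364.3% |
| No effect, 0 | -100% | 0% |

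The printed rule would show a decrease with an interval spanning zero next to a p-value of 0.0098. With the exponential, the interval excludes 0% exactly when the t-test is significant, as it should.

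**Step 4: the robustness analysis**

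The same formula is applied to the median of the log differences, so the same error follows. Separately, the estimate that corresponds to a signed-rank test is the Hodges-Lehmann estimate. The sample median targets the same quantity only if the differences are symmetrically distributed, so the planned estimate and interval need not agree with the planned test.

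**The case against.** The strongest objection is about the text itself. The formula was read from a PDF by a program, and a lost e with a superscript x would leave exactly this string. That it appears twice is limited evidence, since the same notation would have been read the same way each time. Against this, nothing in either place hints at an exponential, and superscripts elsewhere in the document (cm², for example) came through. The original should be checked, but the document at hand states the rule without the step.

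Second, the intention is clear: (x-1)*100 is the ordinary conversion for a ratio, and section 10.2 gives the right mapping, so x may have been meant as the back-transformed ratio. This is the likeliest origin of the slip. It does not rescue the text, because section 10.3.2 applies the formula to values on the log scale, and the correction is the same on either reading.

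Third, a competent programmer would notice a rule that turns equality into -100%, and no analysis program is shown that contains the error. That is fair: the damage is conditional on the rule being followed. A prespecified primary estimator should still not depend on the analyst overriding it.

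Fourth, no inference changes. This stands in full: success is decided by the two-sided test on the log scale. The choice of estimator for the signed-rank analysis is also a secondary matter, and the point does not rest on it.

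**Conclusion.** The formula is wrong as written in both paragraphs of section 10.3.2 and contradicts section 10.2. At the planning values it reports -10% (95% CI -74% to +54%) where the result is +146% (95% CI +30% to +364%). The interval figures assume that the trial observes exactly a log difference of 0.90 with SD 1.00 in 12 patients; the error in the formula does not depend on those values. The claim also assumes that the printed formula is a faithful reading of the original. The fault is confined to the reported estimates and intervals of the primary and robustness analyses. It should nevertheless be corrected before any analysis, because it can reverse the sign of the primary result as reported.

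**What to change.** Check the formula in the original PDF. If it reads the same there, replace it in both paragraphs of section 10.3.2 by x -> (exp(x)-1)*100, where x is the difference of natural logs, and say explicitly that natural logs are used. Confirm that the analysis program, including the one for any interim analysis, uses this version; entering x = 0 should return 0% and x = 0.90 should return about 146%.

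Two further edits are worth making at the same time, though the correction does not depend on them:

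- For the signed-rank analysis, report the Hodges-Lehmann estimate with its matching 95% interval, back-transformed in the same way.
- State success as the lower 95% limit of the back-transformed effect lying above 0%. This keeps the two-sided 5% level and makes explicit the direction already hypothesised at the start of section 10.

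The cost is one formula in the protocol and a check of the program. The sample size, the test and data collection stay as they are.

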| Study
Procedure              | 
Invasive procedures:
 
 
• Biopsy Nr. 1: mandatory biopsy, required for EHSG-KF production
 
• Biopsy Nr. 2-5: facultative biopsies before and after debridement for histological examination of the wound bed
 
• Blood samples for screening lab test
 
• Blood samples for routine lab test
 
• Grafting of EHSG-KF / STSG
 
 
Optional Invasive procedures:
 
 
• Optional biopsy Nr. 6-9: optional biopsy for routine histology and immunohistochemistry at visits 8 and 10
 
 
Non Invasive procedures:
 
 
• Physical examinations
 
• Elasticity assessment of the skin
 
• Colour assessment of the skin
 
• Photographic documentation of study areas
 
• Questionnaires 
 
○ POSAS for all patients
 
○ EQ-5D and BSHS-B for patients <math>\geq 18</math> years
 
○ EQ-5DY and PedsQL for patients <math>< 18</math> years
 
 
 
 |
| Statistical
Considerations:  | 
 
• The primary endpoint (ratio of covered area to biopsy site / donor site surface area at 4 weeks post-grafting) will be analysed after logarithmic transformation by a one sample t-test at significance level of 5%
 
• Assuming a standard deviation of 1.00 for the paired difference between the 2 log (ratios), a sample size of 12 evaluable patients would be required in order to achieve a power of 80% to detect a treatment effect corresponding to an increase of 145% with EHSG-KF (i.e. to a difference of 0.90 on a logarithmic scale) when using a one-sample t-test at two-sided significance level of 5%. This calculated number may be inflated to 15 randomised patients in order to cover for possible drop-outs before the assessment of the primary endpoint.
 
                                                                                                                                                                                                                                                                                              |

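### The robustness analysis tests with the signed-rank test but takes its estimate and limits from the median of the differences, so p-value and interval need not agree

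*Protocol*

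**What the plan says.** The primary analysis in section 10.3.2 is a one-sample t-test on the within-patient difference between log(ratio) on EHSG-KF and log(ratio) on STSG. Success depends on that test alone: "A claim of study success will be made when the two-sided test of the primary endpoint passes the significance level of 0.05".

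To check robustness, the same difference "will also be tested with one-sample Wilcoxon test (signed-rank test"). The next sentence gives the estimate and 95% limits that are meant to go with this test; they "will be derived from the median of this difference by applying the transformation" to a percentage increase. The section mentions neither the Hodges-Lehmann estimate, nor a pseudo-median, nor the method for the limits.

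The planning values are in section 10.2: "Assuming a standard deviation of 1.00 for the paired difference between the 2 log(ratios"), an effect equal "to a difference of 0.90 on a logarithmic scale", and 12 evaluable patients. The synopsis allows up to 15 randomised patients.

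**The concern.** Each rank or sign test has its own estimate and interval, obtained by inverting the test. For the signed-rank test these are the Hodges-Lehmann estimate (the median of all pairwise averages of the differences, the Walsh averages) and limits read from the ordered Walsh averages. The sample median with order-statistic limits belongs to the sign test, which uses only the signs and is less efficient when the differences are close to normal.

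The protocol presents the signed-rank p-value and the median-based interval as a matched pair. Read plainly they are not, and they can give opposite answers on the same data. The purpose of this analysis is to say whether the t-test result survives a weaker distributional assumption. A p-value below 0.05 printed beside an interval that includes no effect, or the reverse, makes that answer harder to report.

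**Working it through.** **1. The plan's own figure.** Inputs from section 10.2: difference 0.90, SD 1.00, two-sided 5%, one-sample t-test. The noncentrality is 0.90 × √n / 1.00. Power is 76.7% at n = 11 and 81.0% at n = 12, so the stated 12 patients for 80% power is reproduced.

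**2. Exact rules at n = 12.**
- Signed-rank test: there are 12 × 13 / 2 = 78 Walsh averages. The exact two-sided test rejects when min(W+, W−) ≤ 13 (attained alpha 4.25%). Its matching interval runs from the 14th smallest to the 14th largest Walsh average.
- Median with order-statistic limits: the interval runs from the 3rd to the 10th ordered difference. It excludes zero when at most 2 of the 12 differences lie on one side. Under the null that probability is 2 × (1 + 12 + 66) / 4096 = 3.9%, so coverage is 96.1%. This is the sign test.

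**3. How often the two disagree under the planning values** (normal, mean 0.90, SD 1.00; simulated).
- Signed-rank test significant: 77% of trials.
- Median interval excludes zero: 62%. As an exact check, a single difference is negative with probability Φ(−0.90) = 0.184, and the probability of at most 2 negatives in 12 is 0.087 + 0.236 + 0.292 = 0.615.
- Significant p-value, interval includes zero: about 17%.
- Non-significant p-value, interval excludes zero: about 2%.
- Total disagreement: about 19%.
- Mean interval width: 1.58 for the median against 1.32 for the signed-rank interval, and 1.58 / 1.32 = 1.20.
- Hodges-Lehmann limits against the signed-rank test: 0% disagreement, as must be the case without ties or zeros.

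At n = 15 under the same values, disagreement is again 19.0%.

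**4. Other shapes (assumed, not from the protocol), n = 12, mean 0.90.** Left-skewed differences (reflected exponential, SD 1): 15.1%. Heavy-tailed differences (t with 3 degrees of freedom, scaled to SD 1): 9.5%.

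**5. Constructed examples, n = 12, one in each direction.**
- Differences −0.35, −0.20, −0.10, 0.40, 0.60, 0.80, 0.95, 1.10, 1.30, 1.50, 1.80, 2.10. Here W− = 3 + 2 + 1 = 6 and the exact signed-rank p is 0.007. The median is 0.875 with limits −0.10 to 1.50. Exponentiated, that is +140% (−10% to +348%), which includes no effect. The Hodges-Lehmann estimate is 0.85 (0.30 to 1.375), in line with the test.
- Differences −2.5, −2.2, then 0.1 to 1.0 in steps of 0.1. Here W− = 12 + 11 = 23 and p is 0.233, yet the median limits 0.10 to 0.80 exclude zero. The Hodges-Lehmann limits, −0.90 to 0.70, do not.

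**The case against.** **The protocol does not name the interval method.** That is true, and an analysis plan not shown here could define the median as the Hodges-Lehmann pseudo-median. The figures above are therefore conditional on order-statistic limits. But section 10.3.2 itself names both the test and the quantity from which the estimate is taken, and in plain wording the median of the difference is the sample median. An analysis plan that follows the sentence inherits the mismatch; one that uses Hodges-Lehmann departs from it.

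**The consequence is limited.** This also stands. Success rests on the t-test alone. Some 17 of the 19 points are in the conservative direction, a wider interval beside a significant p-value. If the differences are symmetric, median and pseudo-median are the same parameter, so what is lost is precision and coherence, not the target. The largest figure comes from the normal case, where a robustness check is least needed.

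**A stronger reading is tempting.** A reader might infer that this is the trial's only safeguard against skewed data and that the check becomes uninterpretable. The documents do not support that. Section 10.2 gives means and SDs of single-arm log ratios and does not show the paired log differences to be skewed; the log transformation is itself a measure against skewness; and the signed-rank p-value remains a valid check whichever interval is printed next to it.

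**The median may cope better with graft loss.** Section 1.1.2 reports one phase I patient with 100% graft loss. An EHSG-KF site with no healed area has a ratio of zero and no finite logarithm. If two such patients among 12 are ranked lowest, 12 + 11 = 23 of the 78 Walsh averages are unbounded, and so is the Hodges-Lehmann lower limit (the 14th smallest). The limits x(3) to x(10) stay finite. That is a real, small drawback. But W− is then at least 23, so the signed-rank test cannot be significant in favour of EHSG-KF, and the unbounded limit agrees with it. If the other ten differences are positive, the median limits exclude zero against p = 0.23, which is the very contradiction at issue.

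**Conclusion.** The point holds as a mismatch within a supportive analysis. Read plainly and with order-statistic limits, the interval in section 10.3.2 belongs to the sign test while the p-value belongs to the signed-rank test. At the planning values the interval is about 20% wider than the matching one, and the two results disagree in about 19% of trials (about 17% significant with an interval including no effect, about 2% the reverse). Under the two assumed non-normal shapes the disagreement is about 10% to 15%. The size depends on the interval method, which the protocol leaves unnamed, and on the assumed distribution.

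It should not be read as a threat to the primary result: the t-test, its interval, the sample size of 12, alpha and the success rule are untouched. This is a minor correction, worth making because it is free.

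**What to change.** In the robustness paragraph of section 10.3.2, replace the median of the difference by the Hodges-Lehmann estimate of the difference, with exact 95% limits obtained by inverting the signed-rank test, back-transformed to a percentage increase. The sample median may be kept as a descriptive statistic without being presented as the estimate that belongs to this test. If the median is preferred as the estimate, the coherent alternative is to pair it with the sign test, at the cost in power shown above (62% against 77% at the planning values).

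The cost is one phrase and standard software output, with no new data and no change to the sample size or the success rule. The one thing to accept is an unbounded lower limit if two or more of 12 patients have complete loss of the EHSG-KF graft and are ranked lowest.
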